## Abstract

Background: Gastrointestinal discomfort affects up to 70% of individuals with spinal cord injury (SCI), largely due to gut dysbiosis caused by altered transit time and reduced gastrointestinal motility from autonomic disruption. Emerging evidence links prebiotics and probiotics to improved microbiome balance and reduced inflammation, yet data in SCI remain limited. Methods: Individuals aged ≥ 18 years, with a chronic SCI (≥1 year) experiencing significant gastrointestinal symptoms, will be invited to participate in this single-center randomized controlled crossover trial. Persons currently taking antibiotics, who have relevant eating or digestive disorders, or who have undergone a recent diet change will be excluded from the study. Participants will be randomized (1:1) into two groups. The first group will take a probiotic (Biotics-G, Burgerstein AG, Rapperswil-Jona, Switzerland) supplement for eight weeks, then after a four-week washout period, they will take a prebiotic (Oat Bran, Naturaplan, manufactured by Swissmill, Zurich, Switzerland) supplement for another eight weeks. The second group will receive the supplements in reverse order. The primary outcome is the Gastrointestinal Quality of Life Index, a questionnaire to assess quality of life related to gastrointestinal disorders. Secondary outcomes consist of gastrointestinal transit time, inflammatory blood markers, and gut microbiome composition. Ethics: The study will be conducted in accordance with the Declaration of Helsinki. The study was approved by the Ethics Committee for Northwest/Central Switzerland (EKNZ, ID: 2025-00238, 24.02.2025, Version 2.0). The study is registered at ClinicalTrials.gov (ID: NCT06870331, 02.04.2025). Written informed consent will be obtained from all participants involved in the study.

## 1. Introduction

In some countries, it has been reported that up to 70% of individuals with a spinal cord injury (SCI) suffer from gastrointestinal (GI) symptoms [1,2,3]. Symptoms like fecal incontinence, abdominal bloating, constipation, and irritable bowel syndrome can substantially compromise quality of life by limiting social participation and psychological well-being. Consequently, previous research has found bowel management to be a top priority among individuals with SCI [4,5]. Bowel management is crucial in recovery and rehabilitation as it majorly affects autonomy and dignity [4,6].

SCI disrupts the bidirectional communication of the central and enteric nervous system, which impairs motor and autonomic output but also disturbs sensory feedback and neuroimmune signaling, all of which contribute to altered enteric nervous system activity [7].

Disruption of neural pathways and autonomic imbalance after the onset of SCI can lead to impaired colonic motility, delayed colonic transit time, and increased barrier permeability in the intestine [8,9,10,11]. These factors contribute to gut dysbiosis and intestinal inflammation, which is increasingly recognized as both a consequence of and contributor to GI complications in SCI [12,13,14]. GI homeostasis, including digestion, nutrient absorption, immune modulation, and barrier integrity, is dependent on the gut microbiome composition [15,16]. A systematic review has recently shown differences in gut microbiota composition in individuals with various GI diseases compared to individuals without GI diseases, which manifest as reduced beneficial bacteria and increased inflammation-associated genera [17]. Gut-derived inflammation may add to systemic immune dysregulation, which can impair wound healing, increase risk of infection, and potentially interfere with neuroregeneration [18]. Further exacerbating these issues is the fact that individuals with SCI often do not adhere to nutrition recommendations, which could worsen their GI complications [19,20,21].

Current bowel care programs, including medications and evacuation techniques, are tailored to symptom management of neurogenic bowel dysfunction focused on regular bowel movements and adequate stool consistency, rather than addressing the root of GI discomfort as well [22]. Probiotics, live microbes that add helpful strains to the gut microbiome, and prebiotics, which promote the growth of beneficial bacteria, hold potential as therapeutic avenues to restore gut microbiota balance after SCI [10,23,24]. Most positive findings regarding improved gut microbiota balance are from studies on non-disabled individuals. During probiotic supplementation, a relative higher abundance of the ingested strains in the gut can be observed [25,26,27,28]. Furthermore, anti-inflammatory effects of probiotics could be proven for various probiotic strains; the exact effect however is strain-dependent and can lead to an improved gut barrier, decreased intestinal permeability, and a decrease in GI symptoms [25,26,29,30]. Studies on probiotic effects on irritable bowel syndrome also showed improved GI symptoms alongside microbiome changes, suggesting a direct link, which could extend to other bowel diseases [31,32,33]. Currently, there is limited evidence available specific to SCI. A cross-over pilot study involving wheelchair athletes, of whom 11 had a SCI, demonstrated good tolerance of both probiotic and prebiotic supplementation [34]. Out of fourteen participants, only one reported minor side effects. Further analyses indicated a positive effect of probiotics on gut microbiome composition and inflammatory status [35], though there was no improvement in subjective GI health [34]. However, higher microbiome diversity has been shown in athletes compared to non-athletes [36,37,38], which may indicate lower inflammatory status and fewer GI symptoms in athletes. This could potentially blunt the effects of probiotics.

To accurately assess the potential of probiotic and prebiotic supplementation in alleviating GI discomfort, it is essential to conduct an intervention study in the broader population with SCI—particularly among those suffering from GI-related complications. The primary objective of this study is to evaluate the effect of probiotic and prebiotic supplementation in improving GI health in individuals with chronic SCI experiencing GI complaints, as measured by the Gastrointestinal Quality of Life Index (GIQLI). As secondary aims, further effects on GI health, including changes in gut microbiome composition, inflammatory serum markers, and GI transit time (GITT) will be assessed. Probiotic supplementation is hypothesized to improve GIQLI scores and decrease GITT and inflammatory serum markers, as well as increasing the relative abundance of beneficial microbial strains and decreasing inflammation-associated genera in the gut.

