### 2.3. Intervention

The probiotic intervention involves an 8-week supplementation with the commercially available probiotic BIOTICS-G (Burgerstein AG, Rapperswil-Jona, Switzerland). Participants take one sachet (2.5 g) daily, mixed into 50–100 mL of water 30 min before breakfast or dinner. Biotics-G supplies fourteen lactobacilli and bifidobacteria strains together with Saccharomyces boulardii, delivering 2.5 × 10^9^ CFU per sachet. The composition closely mirrors Bactosan^®^ Pro-FOS, which improved microbial diversity and reduced systemic inflammation in a crossover pilot study involving wheelchair athletes with spinal cord lesions [35]. Bactosan^®^ Pro-FOS is no longer on the Swiss market, which is why the alternative probiotic BIOTICS-G had to be chosen. The present trial extends that evidence to a community cohort.

The prebiotic intervention involves taking a prebiotic supplement for 8 weeks. The participants take 5 g of oat bran daily (Oat Bran, Naturaplan, manufactured by Swissmill, Zurich, Switzerland), mixed in with their usual breakfast or dinner.

The probiotic supplementation serves as the intervention of interest and the prebiotic supplementation as an active comparator, based on the literature and a pilot study [35,43].

Participants are instructed to maintain their usual training routine and diet, to minimize the chance of potential health modifications to be attributable to any factor other than the intervention with pre- or probiotics. Participants receive weekly reminders to take supplements and are asked to return empty packages to the study center after the intervention periods as a means of control of adherence to supplementation.

The first intervention phase is followed by a 4-week washout period to prevent carryover effects. Previous studies in non-disabled individuals have proven 1–2 weeks to be sufficient for effects of inulin-type fructans (prebiotics) to disappear after the intake has ceased [44]. To ensure adequate washout in our study population, the washout period is extended to four weeks.

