### 2.4. Assessments

Outcome data are gathered at four timepoints: baseline (T1), after the first eight-week intervention phase (T2), after the four-week washout (T3), and after the second intervention phase (T4) - an overview can be found in Table 1. The primary endpoint is the GIQLI, indicating changes in subjective GI health [45]. The GIQLI is a questionnaire consisting of 36 questions assessing health-related quality of life in GI disorders, each on a scale from 0 to 4 [46]. It captures a person’s own perception of symptoms, functional limitations, and the psychosocial impact thereof. The GIQLI can range from a score of 0 to 144, with higher scores indicating better gut health and satisfaction with gut health.

Secondary endpoints cover gastrointestinal transit, systemic and mucosal biology, and safety. GITT is measured in the home setting with the Blue Dye Method, defined as the interval between ingestion of blue food coloring on an empty stomach and the first and last appearance of blue-colored stool [47,48]. Blood serum collected at each visit is analyzed with the Olink Target 48 Cytokine panel (Olink Proteomics AB, Uppsala, Sweden), which quantifies 45 inflammation-related proteins, including cytokines and chemokines such as IL-2 and TNF-α. These markers have been shown to be elevated in the serum of individuals with chronic SCI patients compared to healthy controls [49]. Fecal microbial community structure is characterized by full-length 16S rRNA gene sequencing on the MinION Nanopore sequencer (Oxford Nanopore Technologies, Oxford, UK). DNA is extracted with the QIAamp PowerFecal Pro DNA kit (QIAGEN, Hilden, Germany) using ten-minute bead-beating with 0.1 mm zirconia beads, quantified with Qubit™ 4.0 dsDNA HS fluorimeter (Thermo Fisher Scientific, Waltham, MA, USA), and prepared with the MinION Nanopore Ligation Sequencing Kit (SQK-LSK114) plus native barcodes (EXP-PBC096) (Oxford Nanopore Technologies, Oxford, UK). Libraries are pooled equimolarly, loaded on R10.4.1 flow cells, and base-called with Dorado; reads below a quality score of 9 are discarded. Emu assigns taxonomy. Supplement tolerance and all adverse events are documented throughout the study.

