Variables that may influence these outcomes are captured systematically. At T1, each participant provides age, sex, lesion level and completeness, time since injury, body mass, and current medication (Appendix, Table A1) Physical activity is quantified with the Leisure-Time Physical Activity Questionnaire for persons with SCI (LTPAQ-SCI) [50], while autonomic function is evaluated with the ISAFSCI (second edition, 2021) tool [51]. Dietary intake is recorded with a three-day diary before every visit and processed in Prodi 7.4 (Version 7.4, Nutriscience, Stuttgart, Germany); mean energy, fiber, saturated fat and alcohol intakes are used in sensitivity analyses to mitigate dietary confounding.

Sample logistics follow a standardized pipeline. During the week preceding each visit, participants collect stool in the OMNIgene^®^ GUT (DNA Genotek, Ottawa ON, Canada) and draw 4.9 mL of venous blood into an S-Monovette Serum tube (Sarstedt, Sevelen, Switzerland). Blood is centrifuged within thirty minutes at 1800× *g*, 20 °C, for fifteen minutes. Plasma is aliquoted in 500 µL volumes and stored at −80 °C. Stool is vortexed on arrival, subdivided into 250 µL aliquots, and frozen at −80 °C. To align sampling with supplementation phases, T1 occurs one week before tablets or oat bran are first taken, providing sufficient time to complete home procedures. Thereafter, all home collections take place in the week before each center visit, so that the full protocol spans 21 weeks although active supplementation occupies 20 weeks. Participants receive weekly electronic reminders covering supplement intake, as well as the timing of stool, diary, and GITT procedures.

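### The microbiome hypothesis is worded at strain level, which the assay and named analyses do not resolve, and stool collected during intake lets fed bacteria support its first half

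*Protocol article*

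**What the plan says.** The secondary microbiome hypothesis (1. Introduction) is that the probiotic has the effect of "increasing the relative abundance of beneficial microbial strains and decreasing inflammation-associated genera in the gut". The same section notes that anti-inflammatory effects depend on the strain, and that ingested strains are seen at higher relative abundance while a probiotic is being taken.

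On the product, section 2.3 states: "Biotics-G supplies fourteen lactobacilli and bifidobacteria strains together with Saccharomyces boulardii". The daily sachet delivers 2.5 × 10^9 CFU.

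On the assay, section 2.4 states: "Fecal microbial community structure is characterized by full-length 16S rRNA gene sequencing on the MinION Nanopore sequencer". It adds that "reads below a quality score of 9 are discarded" and that "Emu assigns taxonomy". No strain-resolving or fungal assay is named.

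On timing, section 2.4 says that after T1 "all home collections take place in the week before each center visit". Table 1 puts T2 at week 8 and T4 at week 20, each at the end of an eight-week intake phase.

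On analysis, section 3 (Data Analyses) compares diversity indices with paired t-tests and relates inflammatory proteins, microbial genera, GIQLI and transit time by sparse partial least squares. It also compares the pre-period baselines to check that the gut returned to its starting state during washout.

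**The concern.** Two parts of the article do not fit together. The hypothesis is about strains, while the measurement and the named analyses work at species level at best and mostly at community or genus level. A product strain cannot be told from a resident strain of the same species, and one named component of the product, the yeast, is not measured at all. As worded, the hypothesis cannot be tested.

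Sampling during intake adds a problem of interpretation. Swallowed bacteria, live or dead, leave DNA in the stool. If fed lactobacilli and bifidobacteria are more abundant at the end of the probiotic phase, that may show only that the sachet was taken. Oat bran delivers no bacteria by design, so this contribution exists in one period only. The same genera can then enter the multi-omics model, where a marker of intake could be read as a change in the resident gut community linked to inflammation or symptoms.

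**Working it through.** The article gives no figure for this point that could be reproduced. Three checks apply.

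**1. Resolution.** The hypothesis needs strains. The assay gives 16S reads assigned by Emu, and the analyses use diversity indices and genera. A read at the Q9 floor has an error rate of 10^(−9/10) = 0.126 per base. For an assumed gene length of 1,400 to 1,550 bases that is 0.126 × 1,400 ≈ 176 to 0.126 × 1,550 ≈ 195 errors. This is the worst read admitted, not the typical one: at Q20, 1,500 bases carry about 15 errors. The strain limit does not rest on the quality floor, because strains of one species differ little in this gene. That point, and the fact that a yeast lacks the bacterial 16S gene, are general assay knowledge and are not stated in the article.

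**2. Timing.** Take day 0 as the first dose. Intake is then days 0–55 and 84–139, with washout on days 56–83.
- If T1 is one week before the first dose (section 2.4), or if week 1 of Table 1 is the first week of intake, T2 is day 56 and T4 is day 140. Stool is collected on days 49–55 and 133–139, so 7 of 7 days fall within intake.
- If week 1 of Table 1 is the week before the first dose, T2 is day 49 and T4 is day 133. Stool is collected on days 42–48 and 126–132, again 7 of 7 days within intake.

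**3. Size of the pass-through.** Only the 2.5 × 10^9 CFU per day comes from the article. Everything else here is an assumption.
- Share = CFU × recovery / bacteria passed per day.
- Outputs of 2 × 10^13 and 5 × 10^12 per day with full recovery give 2.5 × 10^9 / 2 × 10^13 = 0.0125% and 2.5 × 10^9 / 5 × 10^12 = 0.05%.
- With outputs from 10^12 to 2 × 10^13 and recovery from 1% to 100%, the range is 0.000125% to 0.25%.
- At 50,000 reads per sample, 0.0125% and 0.05% are 6.25 and 25 reads in total. Over fourteen strains that is 0.45 and 1.8 reads each.
- With an equal split and Poisson sampling, the expected number of product taxa seen is 14 × (1 − e^(−reads/14)). This gives 14 × (1 − e^(−0.446)) ≈ 5 and 14 × (1 − e^(−1.786)) ≈ 12. Against an assumed observed richness of 150 that is about 3% to 8%, provided that every product taxon was absent at baseline, was correctly assigned and is a separate species.
- Across the wider range, 0.000125% is 0.06 reads (nothing seen) and 0.25% is 125 reads (about 9 per strain, so nearly all fourteen seen).
- For Shannon diversity, adding a share p spread evenly over 14 new taxa raises the index by at most −p ln p − (1 − p) ln(1 − p) + p ln 14. At p = 0.05% this is 0.0038 + 0.0005 + 0.0013 ≈ 0.006. At p = 0.25% it is 0.0150 + 0.0025 + 0.0066 ≈ 0.024. Both are negligible in practice.

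**The case against.** A reader might infer that product passing through the gut would count as trial success on the microbiome. The article does not support that. It sets no microbiome success criterion, and the only microbiome comparison that it names is on diversity indices, which pass-through hardly moves. The hypothesis also requires a fall in inflammation-associated genera, which swallowed lactobacilli do not directly produce. Transit can serve the first half only.

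Nor does it follow that the comparison is tilted toward the probiotic overall. The Introduction says that prebiotics promote beneficial bacteria, so oat bran has an expected rise of its own.

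Sampling during intake is a legitimate choice for an effect during use, and the Introduction is open about what to expect then. An off-product sample exists at T3. It follows the probiotic only in the probiotic-first group (planned 25), however, and section 3 treats persistence there as carryover, so it does not settle the question.

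Lists of target taxa and filtering rules may stand in a fuller protocol or analysis plan that is not shown, so their absence is no fault here. The article also nowhere claims to measure the yeast.

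Finally, removing the product's species removes resident bacteria of the same species too, possibly those that oat bran is meant to promote, and changes the denominator of every relative abundance. This objection stands in full: a filtered community should not become the basis for the conclusion.

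What these arguments leave untouched is the mismatch between the printed hypothesis and the printed assay and analyses, and the fact that end-of-phase stool cannot separate fed bacteria from residents of the same species.

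**Conclusion.** The hypothesis is worded at a level that the assay and the named analyses do not reach, and the yeast in the product is outside the assay. Because T2 and T4 stool is collected wholly during intake, a rise in the fed taxa could support the first half of the hypothesis without any change in the resident community. The effect on overall diversity is likely negligible. For single taxa the size ranges from nothing to a clear change from absent to present, depending on stool output, recovery, read depth and baseline rarity, none of which the article gives.

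This concerns the wording and interpretation of a secondary outcome. The primary GIQLI comparison and the sample size of 50 are unaffected. It is worth correcting because the change is cheap and, with data collection planned until summer 2027, can be fixed before analysis.

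**What to change.** - In the Introduction, restate the hypothesis at species or genus level and note that Saccharomyces boulardii is not measured by the planned assay.
- In section 3, list the product's bacterial species in advance and report their abundance at T2 and T4 separately, as a marker of intake. This may also supplement the check of returned packages.
- Keep the full-community analysis as planned. Repeat the genus-level and multi-omics analyses with the product's species removed, as a prespecified sensitivity analysis.
- Claim a change in the resident community only if it holds in both versions.

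The cost is some rewording and a filtering step on data already being collected, with no new samples or assays. The downside is a little more analysis, and a filtered version that also drops resident bacteria of the same species. It should therefore accompany the full-community result and not replace it.

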## 2. Materials and Methods

### 2.1. Study Design, Setting, and Sample Size

This is a single-center open-label two-arm randomized controlled crossover superiority trial (RCCT) adhering to CONSORT guidelines [39] with a total duration of 20 weeks (Supplementary Material). The study is conducted at the Swiss Paraplegic Research in Nottwil, Switzerland. It involves two 8-week interventions consisting of daily intake of either a probiotic (Biotics-G, Burgerstein AG, Rapperswil-Jona, Switzerland) or a prebiotic (Oat Bran, Naturaplan, manufactured by Swissmill, Zurich, Switzerland) supplement, separated by a 4-week washout period (Figure 1). Group allocation, which determines the order of supplement intake by the participants, is determined using a permuted block randomization (block size 4). For this, a randomization list was created using the statistical software Stata (Stata. Version 18. College Station, TX, USA: StataCorp, 2024). Due to the nature of the supplements, no allocation concealment or blinding of study personnel or participants is possible. Recruitment for this study started in summer 2025, and data collection will continue for two years; the study is therefore expected to end in summer 2027. The low-risk nature of this study warrants a risk-based approach for study monitoring. The study will be conducted in accordance with the Declaration of Helsinki. The study was approved by the Ethics Committee for Northwest/Central Switzerland (EKNZ, ID: 2025-00238, 24 February 2025, Version 2.0). The study is registered at ClinicalTrials.gov (ID: NCT06870331, 2 April 2025). Written informed consent will be obtained from all participants involved in the study.

The sample size was calculated for the primary outcome (changes in GIQLI) based on the results of a previous pilot study [34], applying a clinically relevant mean difference of 10 points on the GIQLI [40,41,42] and correcting for a larger expected variability in the GIQLI in the current study population. Assuming a significance level of 5% and a power of 85%, a sample size of 50 participants, with 25 participants in each group, was determined.

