### 2.2. Study Participants

Adult (≥18 years old) male and female individuals with chronic (>1 year) traumatic and non-traumatic SCI, with a complete or incomplete lesion according to the American Spinal Injury Association Impairment Scale (AIS A-D), are invited to participate. Individuals experiencing significant GI complaints, indicated with ‘yes’ at screening and a GIQLI score below 110 at baseline (T1), are included. Exclusion criteria are antibiotic use, major dietary changes within 4 weeks before the study, presence of a diagnosed clinically relevant medical condition (e.g., Crohn’s disease, diagnosed eating or GI disorders), intake of significant concomitant medication (e.g., immunomodulating therapy, mesalazines), and pregnancy. No concurrent participation in other clinical trials investigating or potentially affecting GI health is allowed. Non-adherence to the supplementation, defined by missing >25% of supplement doses, can lead to exclusion from the trial at the investigator’s discretion.

Potential participants are recruited by distributing the study information and a flyer within the networks of the Swiss Paraplegic Association, the Swiss Paraplegic Centre, and the Swiss Paraplegic Research. In the case of a low recruitment rate, study information will also be spread through community platforms, both online and in magazines (e.g., Paracontact). Interested participants are contacted by phone or in person to perform the screening, where eligibility criteria are assessed, and the participant is informed about the study and what procedures it entails. Written participant information and an informed consent form are provided. After at least 24 h of consideration time, informed consent will be obtained from each participant.

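### The plan gives up allocation concealment because of the nature of the supplements, which confuses it with blinding; this leaves the between-sequence comparisons exposed

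*Protocol article*

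**What the plan says.** All of the allocation text is in Section 2.1 of the protocol article. What is allocated is the sequence of the two supplements, and the article says that it "is determined using a permuted block randomization (block size 4"). The sequence was prepared in advance: "a randomization list was created using the statistical software Stata". The article then states: "Due to the nature of the supplements, no allocation concealment or blinding of study personnel or participants is possible". The trial is single-centre and open-label, and the target is given as "a sample size of 50 participants, with 25 participants in each group, was determined". The article does not say who holds the list, or when an allocation is released relative to the T1 visit.

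Section 2.2 describes entry: "Interested participants are contacted by phone or in person to perform the screening, where eligibility criteria are assessed". Inclusion also needs a self-reported yes to significant complaints and a GIQLI below 110 at T1.

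Section 3 plans mixed models with a random participant effect, fixed effects for intervention and period, and adjustment for the baseline before each period. Sequence and carryover terms are added. If carryover is significant, an analysis of period 1 alone follows, and the article says this will give an unbiased estimate. Participants are analysed where data are available. Section 4 names open-label response bias as a limitation but not selection at enrolment. No section qualifies the statement on concealment.

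**The concern.** Concealment and blinding protect different stages. Concealment means that nobody who decides on enrolment knows the next assignment until the participant is irrevocably in the trial. It is complete before any sachet or oat bran changes hands, so the appearance of the products has no bearing on it. Blinding concerns what people know afterwards, and there the appearance matters. The article applies a reason that is valid only for blinding to both.

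This is an affirmative statement, not a detail that a condensed article leaves to the full protocol. A reader must take it that the trial runs without concealment. The people recruiting could then bring forward, defer or discourage an enrolment according to the next sequence. The two sequence groups would no longer be comparable by design, and the analyses that compare them would lose their basis. Selection at entry cannot be undone later by modelling.

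**Working it through.** The article gives no figure for predictability, so there is none to reproduce. The check asks how much a fixed block of 4 reveals when past assignments are visible, as they are in an open-label trial at one centre.

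**Inputs.** Block size 4 and 50 participants (Section 2.1); 1:1 allocation (Abstract); no strata named. Assumptions: staff know the block size, which is published, and keep track of earlier assignments.

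**One block.** There are 6 equally likely orders of two AB and two BA. The best guess is always the sequence with more places left.

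| Position | Probability that it is certain | Probability that the best guess is right |
|---|---|---|
| 1 | 0 | 1/2 |
| 2 | 0 | 2/3 |
| 3 | 1/3 (first two alike) | 1/3 × 1 + 2/3 × 1/2 = 2/3 |
| 4 | 1 | 1 |
| Sum | 4/3 | 17/6 |

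Per assignment, (4/3)/4 = 33.3% are certain and (17/6)/4 = 70.8% are guessed correctly.

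**Fifty participants.** This is 12 full blocks plus the first two places of a thirteenth.

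- Certain: 12 × 4/3 + 0 = 16, and 16/50 = 32%.
- Guessed correctly: 12 × 17/6 + 1/2 + 2/3 = 35.2, and 35.2/50 = 70.3%, against 50% by chance.

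**What varied block sizes would do.** This was simulated for 50 participants, with a guesser who knows the mix of sizes but not each block's size.

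| Blocks | Certain | Guessed correctly |
|---|---|---|
| Fixed 4 | 32% | 70.3% |
| 4 and 6 mixed | about 6% | about 69% |
| 4, 6 and 8 mixed | about 2% | about 68% |

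Varying the blocks removes nearly all certain knowledge but little of the guessing advantage. It supplements concealment and does not replace it.

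**Where selection by sequence would enter the analyses of Section 3.**

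- Intervention effect in participants with both periods: each person is compared with himself or herself, so a difference in the type of person between AB and BA largely cancels.
- Sequence and carryover terms: these rest on comparing AB with BA participants and are exposed.
- Participants with one period only: because people are analysed where data are available, these enter as between-person information. Withdrawal, or the discretionary exclusion for missed doses in Section 2.2, can produce such cases.
- Period 1 alone: this is a parallel comparison of at most about 25 against 25. Its freedom from bias depends on how allocation was made.

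The documents give no basis for putting a size in GIQLI points on any resulting bias.

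**The case against.** The strongest reply is that only the order of supplements is at stake. Everyone is due to take both, the main contrast is within person, and all models adjust for the pre-period baseline. The period-1 analysis is a conditional sensitivity analysis, and the documents suggest no motive for steering anyone towards one order. Eligibility also leaves limited room for judgement: the GIQLI is self-reported with a numeric cut-off, and complaints are a plain yes. All of this stands, and it limits the severity. It does not make the statement correct. Baseline adjustment deals with measured GIQLI only, and the timing of enrolment remains open to influence.

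A second reply is that the sentence may be loose wording for the fact that everyone knows the supplement once it is assigned, and that the list may in fact be held back. That is possible. In that case correcting the sentence and describing the mechanism would suffice.

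Four stronger readings are tempting but not supported:

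- A reader might infer that staff know every upcoming allocation. That would hold only for a list open to them, and the article does not say who has access. The screening text in Section 2.2 does not show that those who screen see it.
- A reader might infer that blocks of 4 make the sequence predictable in any case. It is partly predictable, and only under the assumptions above.
- A reader might count the check of pre-period baselines among the damaged comparisons. Section 3 describes it as verifying a return to baseline during washout, which reads most naturally as T3 against T1 within participants.
- A reader might infer that laboratory staff and the analyst are unblinded. The phrase about study personnel is broad, but coding of samples and datasets is commonly left to the full protocol or analysis plan.

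**Conclusion.** The concern holds in a limited form. The statement that the supplements make concealment impossible is wrong, and nothing else in the article corrects it. As written, the plan gives up a protection that an open-label trial can have.

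With a hidden list and fixed blocks of 4, 32% of 50 assignments would be certain and about 70% guessable, provided that staff know the block size and follow past assignments. If the list is open, more would be known, but the article does not document this. The main within-person contrast is largely protected. The sequence and carryover terms, one-period participants and the period-1 analysis are not, and the promise of an unbiased period-1 estimate does not sit with a declared absence of concealment. This should be fixed, but it does not undermine the primary comparison.

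**What to change.** 1. Replace the sentence in Section 2.1 so that it says only that blinding of participants and treating staff is not possible, and describe how allocation is concealed.
2. For participants not yet randomised, release each allocation only after consent and confirmed T1 eligibility, including the GIQLI score. A data-capture system, or sealed sequential envelopes that those recruiting cannot reach, would do. Section 2.4 places T1 one week before supplementation starts, which leaves room for this step.
3. As a secondary measure, use a new list for the remaining participants with randomly varied block sizes that are not disclosed. Its main benefit is to remove certain knowledge.
4. If recruiting staff have had access to the list so far, state this in Section 4 as a limitation of the between-sequence and period-1 analyses, and qualify the word unbiased in Section 3.

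The cost is one new list and a minor amendment while recruitment continues, plus someone outside the recruiting team to hold the envelopes if that route is chosen. No additional participants are needed.
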